#### Quality of life

The mean HRQoL questionnaire scores and the prevalence of associated symptoms will also be determined, together with their 95% confidence intervals. HRQoL will be compared with the baseline data using statistical analysis tests for paired data in order to determine the factors associated with a better HRQoL. We will test the normality of the quantitative variables using the Kolmogorov–Smirnov test and will apply Student *t*-tests or Mann–Whitney U tests as appropriate to compare numerical parameters between two groups. An analysis of variance or the Kruskall–Wallis test will be used to compare more than two groups. The association between qualitative variables will be contrasted using the chi-square statistic and associations between quantitative variables will be studied with Pearson correlation coefficients and Spearman’s rho. Linear regression and multiple logistic models will be used to control for the effect of several variables on HRQoL, perceived quality of care, and patient function. All the statistical analyses will be carried out with SPSS (version 21.0; IBM Corp., Armonk, NY) and R software for Windows.

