### Design

This is a single-centre follow-up observational study of cases of CRC diagnosed in the Complexo Hospitalario Univesitario A Coruña (A Coruña, northwest Spain) from 2006 to 2013 (*n* = 1945), previously included in some of our other research projects [15–17]. A quality of life sub-study will be carried out in the patients included in the framework of one of these other projects [17] who have not died at the time of this present study (*n* = 485), in order to assess their current HRQoL and compare it with their baseline HRQoL scores when the CRC was initially diagnosed.

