In addition to the data described above, we will also record information about the HRQoL for the patients in the quality of life sub-study (*n* = 485 CRC patients diagnosed from 2010 to 2013) 3 to 6 months from the time of the CRC diagnosis. HRQoL measurements are also available 1 year after diagnosis for *n* = 214 of these patients, and 2 years after the diagnosis in *n* = 195 patients. For the patients in this sub-cohort who are still alive when this project is carried out, information will be collected about their current HRQoL using the general module of version 3.0 of the *European Organization for Research and Treatment of Cancer* (EORTC) *QLQ-C30* questionnaire [19] which is applicable to all cancer patients. We will also apply the EORTC QLQ-CR29 module which is specific to colon and rectal cancer patients [20].

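### Paired tests against baseline are given the job of identifying factors for better HRQoL, which they cannot do, and the 1-year and 2-year scores have no stated analysis

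*Protocol article*

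**What the plan says.** Under Design, survivors of the HRQoL sub-cohort are followed up "in order to assess their current HRQoL and compare it with their baseline HRQoL scores when the CRC was initially diagnosed". Measurements places that first score 3 to 6 months after diagnosis and adds: "HRQoL measurements are also available 1 year after diagnosis" in 214 of the 485 patients, with 2-year scores in 195.

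Under Quality of life, HRQoL is to be "compared with the baseline data using statistical analysis tests for paired data in order to determine the factors associated with a better HRQoL". The section then moves to methods for separate groups: it "will apply Student *t*-tests or Mann–Whitney U tests as appropriate to compare numerical parameters between two groups", and "An analysis of variance or the Kruskall–Wallis test will be used to compare more than two groups". Chi-square tests and correlations follow, and finally: "Linear regression and multiple logistic models will be used to control for the effect of several variables on HRQoL". The full list of outcomes for those models is to "control for the effect of several variables on HRQoL, perceived quality of care, and patient function".

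The section does not say whether the modelled outcome is the current score or the change, and it does not list covariates. It mentions neither the 1-year nor the 2-year scores. The Discussion expects the results to show whether HRQoL is back to normal 1 year after diagnosis.

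**The concern.** The only sentence of the analysis section that uses the baseline score ties it to a question that the test cannot answer. Read literally, an analyst would report a significant or non-significant mean change as evidence about factors.

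There are two consequences for the rest of the section. First, the methods that can examine factors are not linked to the earlier score. A difference in current HRQoL between groups could then reflect a difference already present at 3–6 months, and precision may be lost in a sub-study of about 200 patients. Second, the Discussion expects an answer about HRQoL at 1 year, while the analysis section names only a comparison of current with baseline scores.

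A smaller point is that perceived quality of care appears as a modelled outcome, but Measurements names no instrument for it.

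**Working it through.** **Sub-study size (reproduced; not in dispute).** Sample size gives 281 expected survivors of 485, 30% losses, 95% confidence and ±7% precision. For a proportion of 0.5 (my assumption; none is stated), n = 1.96² × 0.25 / 0.07² = 196. From the survivors, 281 × 0.70 = 196.7. Both agree with the stated figure of about 200.

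**What the paired test estimates.** Let D be the current score minus the earlier score. The test statistic is mean(D) / (SD(D)/√n), and its null hypothesis is that the mean of D is zero. Take a two-level factor split equally, coded −½ and +½, with effect δ on the current score, and an average change μ. The mean of D is then μ, because δ cancels. The factor only inflates the variance of D, by δ²/4. With an unequal split, the factor shifts the pooled mean but still cannot be separated from μ.

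**Illustration.** The assumptions, none from the documents, are: 196 completers split 98/98, SD 1 at both times, correlation ρ = 0.5, two-sided 5% level, 4,000 simulated data sets.

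| Truth | Paired test rejects | Two-group t-test on current score | Regression with earlier score |
|---|---|---|---|
| Factor effect 0.4 SD, no mean change | 5.1% | 81% | 89% |
| No factor effect, mean change 0.3 SD | 98.6% | about 5% | about 5% |

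The second row can be checked by hand. The variance of D is 2(1 − 0.5) = 1, so the standardised change is 0.3 × √196 = 4.2, and power is Φ(4.2 − 1.96) = Φ(2.24), about 98.7%. The paired test therefore responds to change over time. When a real factor effect is present without mean change, it rejects at its nominal false-positive rate.

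**Size of the adjustment gain.** Adding the earlier score multiplies residual variance by 1 − ρ²:

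- ρ = 0.3: 0.91, a cut of 9%
- ρ = 0.5: 0.75, a cut of 25%
- ρ = 0.6: 0.64, a cut of 36%

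The factor difference detectable with 80% power and 98 per group, without adjustment, is (1.96 + 0.84) × √(2/98) = 0.40 SD. Multiplying by √(1 − ρ²) gives 0.38 SD at ρ = 0.3, 0.35 SD at ρ = 0.5 and 0.32 SD at ρ = 0.6.

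**Data held against analyses named.**

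| Occasion (Measurements) | Analysis named (Quality of life) |
|---|---|
| 3–6 months, n = 485 | Paired comparison with current score |
| 1 year, n = 214 | None, although the Discussion expects a 1-year conclusion |
| 2 years, n = 195 | None |
| Current, about 197 expected | Paired comparison; outcome of the factor analyses is not specified as score or change |

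**The case against.** The strongest reply is that the fault lies in one purpose clause. Comparing current with baseline HRQoL is a stated aim under Design, and paired tests serve it. Between-group tests and multivariable regression are named in the same paragraph and can examine factors, so neither aim lacks a method. This stands, and it limits the harm, but the sentence remains wrong as written. Reading it as paired tests run within each subgroup does not rescue it, because one subgroup changing significantly and another not is no test of a difference between them.

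A reader might go further and infer any of the following. The document does not support them:

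- **That the factor analyses ignore the baseline score.** The regression covariates are unlisted, and the earlier score may be among them. Covariate lists are commonly left to a fuller document. All that can be said is that its use is not stated.
- **That the 1-year and 2-year scores will be discarded.** Silence does not show this. The overlap of those 214 and 195 patients with the respondents is also unknown, since about 485 − 281 = 204 of the sub-cohort are expected to have died. The benefit of a model on all occasions therefore cannot be quantified. The mismatch with the Discussion's 1-year question remains.
- **That adjustment buys a fixed gain,** such as making 197 respondents worth 197/0.75 = 263. That figure needs ρ = 0.5, which the article does not give, and it assumes that no other covariate already explains the same variance.
- **That perceived quality of care was never measured.** Measurements refers to earlier publications for detail, so a source may exist.

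It is also fair to say that adjustment is not neutral. A score taken 3–6 months after diagnosis may already carry treatment effects, so for treatment factors the adjusted and unadjusted models answer different questions.

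**Conclusion.** The point holds in limited form. The stated purpose of the paired tests is wrong, and this follows from the definition of the test without any assumed figure. The factor analyses are not stated to use the 3–6-month score, and the 1-year and 2-year scores have no analysis although a 1-year conclusion is expected.

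The possible gain from adjustment is a 9% to 36% cut in residual variance for assumed correlations of 0.3 to 0.6, and less where other covariates explain the same variance. The simulated rejection rates are illustrative only.

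HRQoL is a secondary aim and usable factor methods are already named, so this should be corrected but does not undermine the study.

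**What to change.** 1. State that the paired tests assess mean change from the 3–6-month score to the current score, and remove the reference to factors from that sentence.
2. For factors, specify a regression of the current score with the 3–6-month score as covariate, or a linear mixed model on all available occasions (3–6 months, 1 year, 2 years, current) with factor-by-time terms. The mixed model would also give the 1-year and 2-year scores a role.
3. For treatment factors, also report the model without the 3–6-month score, and say that the two models answer different questions.
4. State the source of perceived quality of care, or remove it as an outcome.

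The cost is revised wording and a little more analysis. The earlier scores are held. The current scores are still to be collected, but that is already planned, so no further data collection is needed.

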## Discussion

CRC is a major public health problem worldwide and is one of the most common tumour types in terms of its incidence and associated mortality rates [1]. Advances in the diagnosis and treatment of CRC has caused its mortality rates to decrease in recent years, thus increasing the number of long-term CRC survivors [3]. These survivors experience the normal issues related to aging, along with the physical and emotional effects of a cancer diagnosis and of its treatments [25]. Therefore, one goal remains further improvement of the probability of ‘curing’ this disease while also improving the life expectancy for these cured patients.

Thus, large epidemiological studies are important to check the effects of diagnosis and treatment improvements in terms of patient survival, to identify prognostic factors, and to detect subgroups who could need more frequent follow-up surveillance. Therefore, the primary endpoint of this proposed study will be to provide an accurate, updated estimation of long-term survival in CRC patients, as well as to identify variables that may be associated with the probability of a cure and with survival time in uncured patients.

Traditional statistical methods (such as Kaplan–Meier curves or the Cox proportional hazards model) commonly used to estimate survival in CRC patients, implicitly assume that all patients with the same global diagnosis of CRC are at risk of developing the event of interest (e.g., death from the tumour) if they are followed for a sufficiently long period of time. This hypothesis is reasonable when overall mortality is analysed, but falls short when analysing specific-cause mortality or disease-free survival because some patients will never die from the CRC cancer or suffer a recurrence of the tumour. Therefore, alternative survival models taking this into account should be considered.

Statistical cure models could be a useful alternative in this context, even though they are not often currently used in clinical research [26]. Cure models assume that a fraction of the patients will be cured by the treatment and will never be at risk for suffering an event related to the specific disease again (e.g., CRC death, recurrence, or metastases). Therefore, these models might provide a better estimation of the ‘cure fraction’ while also modelling the average time to the occurrence of a new event among uncured patients as well as associated prognosis factors. These models therefore allow the clinical determinants of the cure and the variables associated with survival to be analysed [27].

To the best of our knowledge, this is the first study in Spain employing cure models to analyse the long-term prognosis of CRC patients. Furthermore, no other published studies have evaluated the impact of clinical variables other than age, sex, disease stage, or location on long-term CRC survival by using a similar methodology. The research published to date are mainly cancer-registry population studies that do not include clinically important variables such as those registered in hospital-based cohort studies like this one. Other strengths of this project are its relatively large sample size and the long-term follow-up periods considered.

Health care for long-term survivors must include strategies not only for the early diagnosis of recurrences and new neoplasms, but also to detect the long-term medical and psychological effects of cancer diagnosis and treatments [25]. Thus, characterisation of long-term survivors and analysis of their outcomes will help researchers to assess the adequacy of the medical care provided to them and to optimise the health resources invested in these patients. The secondary aims of this project will be to provide information on the symptoms and HRQoL of long-term CRC patients. These results will allow us to confirm whether, as other authors have indicated, HRQoL returns to normal 1 year after diagnosis [28]. This data could be important to CRC patients, for example, in planning scheduled follow-up visits to screen not only for medical issues, but also for the late effects of treatments on patient HRQoL and symptoms.

Finally, this research is not without limitations. Firstly, it is a single-centre study which includes a sample from only one hospital in Spain. Secondly, some of the measurements were obtained from clinical records, and so the possibility of information bias could not be discarded. This could limit the generalisability of the results and so, future studies including other populations are warranted. Nonetheless, this study reflects the outcomes of real-life practice in a specialised hospital. Moreover, because it is a single-centre study, the procedures, metrics, and variables collected were homogeneous. In summary, this study had a large sample size and long follow-up time and its results are expected to help identify the needs and clinical situation of long-term survivors of CRC and will be useful for proposing new models of care for the follow-up of these patients.

## Data Availability

The datasets that will be used or analysed during this current study are not yet available because the study is presently ongoing. They will be available from the corresponding author upon reasonable request once recruitment and data collection is complete.

## Abbreviations

CRC: Colorectal cancer
HRQoL: Health-related quality of life
